# 4. Study parameters/endpoints

The primary outcome measure is need for recovery. Secondary outcome measures are physical activity, sedentary behaviour and relaxation at/detachment from work. Furthermore, several demographics (i.e. age, gender, education), work and health-related factors will be examined. A subsample will be invited to wear an accelerometer.

# 4.1 Primary outcome measure

Need for recovery will be assessed using the need for recovery after work scale of the Dutch VBBA questionnaire (63). This Dutch version of the Questionnaire on the Experience and Evaluation of Work (Dutch abbreviation VBBA) consists of eleven dichotomous items (yes/no). The VBBA has been evaluated among 601 employees from various organisations in the Netherlands, and showed satisfactory validity (r=0.65) and reliability (r=0.87) (63).

#

# 4.2 Secondary outcome measures

Daily physical activity will be assessed by the Short Questionnaire to Assess Health Enhancing Physical Activity (SQUASH) (69). This questionnaire assesses the duration, frequency, intensity of active home-to-work transport, physical activity at work, sedentary time at work and home, activity in leisure time and household activities, and sport. The SQUASH is a fairly reliable (r=0.58) and reasonably valid (r=0.45) questionnaire. Its validity and reliability are comparable to other physical activity questionnaires (70).

Physical activity and sedentary behaviour will also be measured objectively in a random sample of 100 participants, consisting of the GMI group (n=25), the GMI and environmental modifications group (n=25), the environmental modifications only group (n=25) and the control group (n=25). This subsample will be asked to wear the accelerometer during a period of 7 days, both at baseline, 6 and 12 months follow-up. On all days of the week, participants fill out a short questionnaire (diary) on the exact wearing times of the Actigraph (i.e. the time at which the Actigraph was put on and off) and the times of leaving and arrival at home and work (to determine the exact wearing time at work and leisure time). At the end of each week, they will be asked to hand it back to the researcher/research assistant on appointment.

Detachment and relaxation will be assessed by the recovery experience questionnaire, which is developed by Sonnentag et al. (71) and showed satisfactory reliability (r=0.84) and reasonable validity (r=0.46). A Dutch version of this questionnaire showed high reliability (r=0.92) in a pilot study by Bloom et al. (72). We will adapt this scale to a work context, starting each item with “During a break at work…”, instead of “During time after work…” as written in the original questionnaire of Sonnentag et al. (71). This detachment and relaxation questionnaire consist of 8 items and is derived from the recovery experience scale (71). It consists of items such as “I forget about work”, “I don’t think about work at all”, “I kick back and relax” and “I do relaxing things”. Each item can be scored on a 7-point scale, ranging from “never” to “always”. Both the original and modified version of the recovery experience scale (71) will be assessed.

# 4.3 Other measures

Baseline measurements will include demographic questions, such as age, sex and education level. Other measures that will be asked at baseline, 6 months (T1), and at 12 months (T2) follow-up are described below.

Exhaustion will be assessed by means of a subscale of the Oldenburg Burnout Inventory (OLBI) (73). The OLBI consists of 8 items about exhaustion and disengagement and can be scored on a 4-point scale, ranging from “totally agree” to “totally not agree”. It showed reasonable validity (r=0.52) and satisfactory reliability (r=0.80) in different occupational groups (73).

General health and mental health will be measured by items of Dutch validated version of the Rand-36 (74), which showed satisfactory reliability (r=0.83) and reasonable validity (r=0.49). General health perceptions are measured by asking employees to give an indication on how they perceive their health (on a 5-point scale ranging from "excellent" to "bad") and to indicate on four propositions (e.g. “I fall ill more easily than others”) to which extent they agree "totally" or "totally not agree", on a 5-point scale. To assess mental health, employees will be asked to indicate on a 6-point scale ("always" to "never") how often they felt full of life, worn out, tired and full of energy, during the past four weeks (74).

To measure stress, the short form of the perceived stress scale (PSS; 4 items; 5-point scale "never" to "very often") will be used (75). PSS-4 is considered to be sound, but it has a rather low internal reliability (r=0.60). Both the 10- and 14-item self-report of PSS have higher satisfactory reliability and validity (75). Still, the PSS-4 was chosen for this study because it is not meant as a diagnostic instrument. It will only be used to make comparisons between past and current stress levels.

Sleep quality will be assessed by the Jenkins sleep problems scale. (72) This scale contains 4 items, i.e. trouble falling asleep, continue sleeping, waking up several times at night and waking up feeling tired and worn out. The scale showed an acceptable test-retest reliability (r=0.59) and internal consistency of (r=0.63).

Determinants of behaviour and behaviour change for physical activity and relaxation will be examined by means of the lifestyle behaviour questionnaire (DLBQ), which is validated by Lakerveld et al. (76). Determinants of interest for daily physical activity and relaxation are awareness, knowledge, attitude, subjective norm, self-efficacy, physical environment. The items are measured on a 5-point scale from “totally agree” to “totally not agree” (77;78). A study of Lakerveld et al. demonstrated that the DLBQ is able to measure determinants that precede the intention to change physical activity in adults (73).

Absenteeism data will be collected by questionnaires at 3, 6, 9 and 12 month’s follow-up through self-report, as well as by company registrations. The World Health Organization Health and Work Performance Questionnaire (WHO-HPQ), a self-report measure concerning absenteeism and presenteeism, will be used (79). To illustrate, participants will be asked to give "the number of days missed due to mental or physical health problems, during the last 4 weeks".

Work performance will be assessed with the Individual Work Performance Questionnaire (IWPQ), (80). The IWPQ consists of 20-30 questions in four subscales: task performance, contextual performance, adaptive performance, and counterproductive work behaviour. Answers can be scored on a 7-point scale, ranging from “never” to “always”. The IWPQ is a newly developed instrument based on a review of the work performance literature, existing work performance questionnaires, and expert opinions (80).

Job characteristics will be assessed with 30 items (4-point scale from "totally agree" to "totally not agree") of the validated Dutch version of the Job Content Questionnaire (JCQ), (81) i.e. job demands, skill discretion, decision authority, supervisor and co-employee support and job insecurity. It showed satisfactory reliability (r=0.72). The JCQ is widely used (81) and derived from the well-known Job Demands-Control-Support model of Karasek and Theorell (82).

Work engagement will be measured, using the validated Utrecht Work Engagement scale (UWES ), which assesses vitality (6 items), dedication (5 items) and absorption (6 items) (79). Each item can be scored on a 7-point scale, ranging from “never” to “always”. The concepts vitality, dedication and absorption will give an indication about employees' engagement level (79). The psychometric properties of this questionnaire have been tested and results indicate an acceptable internal consistency of vitality (r=0.68-0.80), dedication (r=0.91) and absorption (r=0.73-0.75) (79).

# ****4.4 Interventions within the VIP program****

The ‘VIP in Insurance’ program encompasses two elements, i.e. (A) Group Motivational Interviewing (GMI), supported by a social media platform, and (B) environmental modifications. The control group will receive no specific interventions and will proceed working as usual. A special VIP page will be created on the intranet for all employees, summing up the current offers of the financial service provider which are related to daily physical activity and relaxation. Furthermore, every two months, all employees will receive a newsletter about the VIP project.

#

# 4.4.1 (A). Group motivational interviewing

In this project, teamleaders will be trained to supervise the GMI-sessions, instead of professionals. The presence of GMI-skills within the company will provide long-term benefits. The teamleaders of the wings allocated to the GMI-intervention will be invited for the two-days training in GMI, which will be conducted by a GMI-professional. Acquired knowledge can be applied to other areas, e.g. yearly assessments of employees. After completing the 2-days training, the VIP-teamleaders will directly start with the GMI-sessions in their team. The teamleaders will conduct three GMI-sessions of 90 minutes each, within a period of 6 weeks (every 3 weeks a session). A booster session will be scheduled, 2 months after the final session. All sessions will take place during work hours. The main aim of all these sessions is to stimulate daily physical activity and relaxation. The key elements of the sessions are to develop discrepancy, roll with resistance, express empathy and support self-efficacy (42). During the GMI-sessions, the team leader will focus on fostering a readiness to change, lowering resistance and ambivalence towards changing daily physical activity and relaxation behaviour. For each session, materials will be developed. There is a manual, which consists of theoretical information and detailed instructions. The VIP-teamleader will supervise the sessions by following the instructions in the manual. Furthermore, when the VIP program is ongoing, the VIP-teamleaders will have two meetings of 90 minutes each, supervised by a GMI-professional, to share experiences with each other.

Session 1 “launch of GMI”

Session 1 will focus on welcoming the employees and creating a warm and trustworthy atmosphere. The agenda of the upcoming GMI-sessions will be explained in this session. Furthermore, the social media platform will be introduced and a competition with a step counter will be explained. Specifically, the employees will receive a step counter and they will be stimulated to raise their steps with 10 percent each week. It is a virtual team competition from Amsterdam to Paris. Also, the employees will be informed on the main subjects of the program, i.e. daily physical activity and relaxation. After this introduction, the employees will be asked to interview each other in pairs on their current physical activity and relaxation behaviour at work. Subsequently, the employees will be asked to fill in a handout, i.e. a timeline of their current physical activity and relaxation behaviour. In addition, they will interview each other in small groups about possible difficulties that could occur when changing their current lifestyle. At the end, homework is given by the GMI-teamleader.

Session 2 “considering physical activity and relaxation behaviour” First of all, the state of the virtual competition from Amsterdam to Paris will be briefly discussed. Then, the employees will fill in a handout about importance, trust and ability to change their physical activity and relaxation behaviour. In pairs, they will discuss their findings. Furthermore, the stages of change concept (83) will be explained by the GMI-team leader and the developed wheel of change map will be showed. Here, employees will mark their stage of change with a chip. Subsequently, employees will be asked to reflect on their own stage, during a group discussion, and to describe how they could change their behaviour. The last assignment of this session is to fill in a hand-out about desire, ability, results and needs. They will be asked to discuss this in pairs and to share their results in the group. Again, homework will be given.

Session 3 “action”

Main aim of this session is to formulate action plans to improve daily physical activity and relaxation. First of all, by means of the wheel of change map, employees will be asked to place their chip on their current position. The results will be discussed in the group. The GMI-team leader will inform the group about the financial service provider's vitality program and the facilities they can use. Then, individual goals will be formulated about improving daily physical activity and relaxation. In addition, a handout about successful change will be filled in and discussed in pairs. After stating the goals, and referring to former success stories, an individual action plan to improve daily physical activity and relaxation will be formulated. This action plan will be discussed in pairs. Homework for the upcoming weeks will be given, such as to follow the individual action plan.

Booster session

After two months, a booster session is scheduled. Again, by means of the wheel of change map, employees will be asked to place their chip on their current position. The outcomes will be discussed and solutions will be introduced by sharing experiences. During a group discussion, employees are asked to evaluate the last two months. Furthermore, employees will be asked to critically evaluate previous sessions by examining formerly filled in handouts. If necessary, the action plan or other hand-outs can be revised. Subsequently, employees will be asked to give each other compliments non-verbally, by means of a handwritten card. The employees will be stimulated by the GMI-team leader to remain improving their daily physical activity and relaxation behaviour. The booster session will end by evaluating the VIP program.

Supporting social media platform

During the GMI-sessions, a social media platform will be available through an external website. The VIP social media platform is meant for both employees and teamleaders, allocated to the GMI-intervention arms of the study. The VIP researcher will send a login-code by email. The main goal of this platform is that employees will create or join physical activity and relaxation groups. Potential activities can be playing on a dartboard, lunch walking, doing physical exercise and taking part in a book club. Employees can create their own groups or they can join other groups who are created by their colleagues. The teamleader can be invited to join the employees on the platform. Furthermore, the employees can find appealing information, which will be continually updated by the researcher of the VIP project. For the teamleaders, there is a separate group on the social media platform where they can share experiences with other teamleaders.

# 4.4.2 (B). Environmental modifications

Environmental modifications will be applied to two departments (six wings). The environmental modifications will focus on facilitating daily physical activity and relaxation in the work environment, by changing the coffee corners, the open office environment, the meeting rooms and the entrance hall. Coffee corners will be adapted by adding bar chairs, magazines on the tables, an electronic dartboard, indoor plants, relaxing lights and by painting the coffee corner walls. In addition, the open office environment will be changed by introducing exercise balls, standing desks, sound masking to reduce background noise, and indoor plants. The interior of the meeting rooms will be changed by placing a stand-up table, a lamp, an indoor plant and by painting the walls. Furthermore, a ping-pong table and an indoor plant will be placed in the entrance hall. Prompts of decisions posters to promote daily physical activity and relaxation will be attached on the walls of the coffee corner and the entrance hall. In addition, food steps will be placed on the floor by the entrance hall to promote stair walking. All these environmental modifications will be promoted by posters in the coffee corner and in the hallway. Furthermore, the employees and the teamleaders will receive information by email about the environmental modifications.

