# 2. Objectives and research questions: VIP in Insurance project

The primary objective of this study is to evaluate the effectiveness of the ‘VIP (Vitality in Practice) in Insurance’ program, i.e. GMI, supported by a social media platform, and/or environmental modifications, on the need for recovery, daily physical activity and relaxation levels in office employees. Secondary objectives are to evaluate the cost-effectiveness and cost-utility of the VIP program and to evaluate the process of implementation of the VIP program.

We hypothesize that the VIP program will significantly lower the need for recovery in office employees by increasing daily physical activity and relaxation, compared to the control group, both at short-term (6 months) and long-term (12 months) follow-up. We expect that the intervention arm with both the GMI-intervention and the environmental modifications will be more successful to lower the need for recovery in office employees, than the intervention arms with only GMI or only environmental modifications.

Research questions

The research questions of the ‘VIP in Insurance’ project are:

1) What are the effects of the VIP program on need for recovery in office workers?

2) What are the effects of the VIP program on daily physical activity and relaxation in office workers?

3) What are the cost-effectiveness and cost-utility of the VIP program from a societal and company perspective?

4) What are the strengths and weaknesses of the VIP program when implementing the program?

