# 3. Methods

# 3.1 Population

The study sample consists of office employees (18-64 years) of a financial service provider in the Netherlands. The building of this financial service provider has 10 departments with 24 wings. Each wing has the capacity for 6 teams, corresponding with a total of 60-80 employees per wing. Wings on a department level are separated from one another. In the present study, teamleaders and their employees of 13 wings will be invited to participate. We decided to exclude 4 departments (11 wings) beforehand, since environmental modifications are already ongoing or planned in these departments.

#

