# 3.3 Design

In this study, a randomized controlled trial design will be employed, with pre-stratification on environmental modifications. That is, two strata will be created, with (6 wings) and without (7 wings) environmental modifications. Within each stratum, wings will be randomly assigned to GMI or no GMI. Randomisation will take place at wing level. We decided to apply cluster randomisation on wing level to avoid contamination with employees in the control group. Consequently, the study will consist of four research arms, i.e. (1) both GMI and the environmental modifications, (2) environmental modifications/no GMI, (3) GMI/no environmental modifications, (4) no GMI/no environmental modifications (control group). The design of the VIP project is shown in appendix 1.

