Randomisation of GMI will be performed after the baseline measurement (T0) and will be prepared and executed by an independent researcher, by using a computer generated list from SPSS. After baseline, extensive (online) questionnaire data will be gathered at 6 months (T1), and at 12 months (T2) follow-up, in both the intervention and the control group. At 3, 6, 9 and 12 months follow-up, data is gathered for the economic evaluation. At 6 and 12 months these questions will be added to the extensive online questionnaire. At 3 and 9 months these questions will be asked separately by a small online questionnaire. Furthermore, at 6 months follow-up (at the end of the intervention) questions to evaluate the program will be added. Reminders for the questionnaires will be sent, after one week. A timeline of the VIP project can be found in Appendix 3.

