# 6. Statistical analysis

First of all, baseline characteristics will be analyzed on differences between the four intervention arms, by two-way analysis of variance for numerical data and chi-square and logistic regression for categorical data. Multilevel regression analyses will be performed regarding the effectiveness of the intervention on need for recovery, the secondary outcome measures physical activity/relaxation and other work and health-related variables after 6 months (short-term) and 12 months (long-term). The intervention effect will be estimated in each stratum and a pooled estimated effect is calculated across strata. Multilevel analysis takes into account the clustering of observations of employees within the same wing. All analyses will be performed crude, and adjusted for possible confounders, such as gender and age. Also, these variables will be checked for effect modification. Correction for baseline values will be applied. Analyses will be carried out to test differences in sick leave between the four study intervention arms. All statistical analyses will be performed according to the intention-to-treat principle. Per protocol analyses will be performed to investigate the effects of the intervention in participants who showed high compliance (>70%) to the GMI intervention. Where necessary, missing data will be imputed using multiple imputation techniques. For all analyses a two tailed significance level of p<0.05 is considered statistically significant. All analyses will be performed with SPSS 19.0 (SPSS Inc. Chicago, Illinois, USA).

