# 6.1 Economic evaluation

The aim of the economic evaluation will be to determine the cost-effectiveness, from a societal and company perspective, of the three intervention arms in comparison with the control group. Furthermore, the cost-utility from the company perspective will be studied. The follow-up will be one year, similar to the trial. The analyses will be performed according to the intention-to-treat principle. Productivity losses, i.e. sick leave and productivity data, will be measured with the Dutch version of the WHO-HPQ and IWPQ, (see secondary outcome measures), and the company registrations. In addition, participants are asked to complete a retrospective questionnaire, measuring health care use and personal costs related to the intervention. All questionnaires will be administered on a three-monthly basis. First, societal costs and company costs will be estimated, and compared between the intervention group and control group. Also, a cost-benefit analysis (CBA) will be performed in which the incremental intervention costs are compared to the incremental costs for productivity losses. Confidence intervals (95%) around the difference in costs will be obtained by bias corrected and accelerated (Bca) bootstrapping. Subsequently, a cost-effectiveness analysis (CEA) will be performed from the company perspective. An incremental cost-effectiveness ratio will be calculated, by dividing the difference between the mean company costs of the four intervention arms by the difference in the mean effects on the primary outcomes of the four intervention arms. Bootstrapped incremental cost-effectiveness ratios will be graphically presented on cost-effectiveness plans. Cost-acceptability curves will be generated, showing the probability for cost-effectiveness of the intervention at different ceiling ratios. Similarly, the CEA from the societal perspective will compare the incremental societal costs with the incremental effects on the primary outcomes. Sensitivity analyses will be done to assess the robustness of the results.

#

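### Only GMI is randomised: combined v GMI-only, combined v control and environment-only v control compare different departments, are not labelled as non-randomised, and have no matching effectiveness analysis

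*Protocol*

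**What the plan says.** **Allocation.** Section 3.3 makes environment a stratification factor: "two strata will be created, with (6 wings) and without (7 wings) environmental modifications". It then says "Within each stratum, wings will be randomly assigned to GMI or no GMI". Section 3.4 describes a randomisation procedure for GMI alone: "Randomisation of GMI will be performed after the baseline measurement (T0". Section 4.4.2 adds the level at which environment varies: "Environmental modifications will be applied to two departments (six wings". No section describes a random step for environment.

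**Departments in the study.** Section 3.1 starts from 10 departments with 24 wings and states: "We decided to exclude 4 departments (11 wings) beforehand, since environmental modifications are already ongoing or planned in these departments".

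**Claims.** Section 2 hypothesises that the VIP program lowers need for recovery "compared to the control group, both at short-term (6 months) and long-term (12 months) follow-up". It also expects the combined arm to do better than GMI alone and than environment alone. Section 3.3 defines the control group as the arm with neither component. Section 6.1 sets out to cost the effects "of the three intervention arms in comparison with the control group".

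**Analysis.** Section 6 states: "The intervention effect will be estimated in each stratum and a pooled estimated effect is calculated across strata". Clustering is modelled within wing, and baseline values are corrected for. Section 6 tests sick leave across the four arms. Section 6.1 uses four-arm differences in mean effects on the primary outcomes as the denominator of the cost-effectiveness ratio.

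**The concern.** The allocation, the hypotheses and the effectiveness analysis do not fit each other. Environment is a property of whole departments, so a comparison across strata is also a comparison of departments. An analysis that works within environment strata and then pools cannot estimate an environment effect, nor the gain of the combination over GMI alone.

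The combination is nevertheless what section 2 expects to do best, and two of the three costed comparisons in section 6.1 cross the strata. Followed as written, the plan has no effectiveness test for half of its combination expectation. Its economic results could present differences between departments as effects of the intervention, under the description of a randomised trial and without a caveat.

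**Working it through.** **1. Units.** From section 3.1: 10 − 4 = 6 departments and 24 − 11 = 13 wings. From section 4.4.2: 2 departments (6 wings) have modifications. That leaves 6 − 2 = 4 departments (13 − 6 = 7 wings) without, which agrees with the strata in section 3.3 and Appendix 1.

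**2. Which contrasts are randomised.** The plan gives no single list. The five below are put together from sections 2 and 6.1.

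| Contrast | Called for in | Within one stratum, so randomised | Estimated by the section 6 effectiveness analysis |
| --- | --- | --- | --- |
| GMI-only v control | 6.1 | yes | yes |
| Combined v environment-only | 2 | yes | yes |
| Combined v GMI-only | 2 | no | no |
| Environment-only v control | 6.1 | no | no |
| Combined v control | 6.1 | no | no |

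The programme-versus-control hypothesis in section 2 is randomised only for its GMI-only part, because the control group lies in the stratum without modifications.

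**3. What the sample size is for.** Inputs from section 3.5: difference 12, SD 29.75, power 0.90; two-sided 0.05 from section 6.
- Per group: 2 × (1.96 + 1.2816)² × 29.75² / 12² = 129.2, so 130, and 260 in total. This reproduces the plan's figure.
- 260 × 1.3 = 338; 338 × 0.9 = 304.2 (stated 305); 305 / 0.75 = 406.7 (stated 404, within 1%).

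This is the size for one two-group comparison, which fits pooled GMI v no GMI. Taking the plan's 1.3 and 0.9 as they stand:
- Pooled GMI: 152.5 / (1.3 × 0.9) = 130.3 effective per group, power 0.90.
- One arm against another: 76.25 / (1.3 × 0.9) = 65.2 effective per arm, SE = 29.75 × √(2 / 65.2) = 5.21, and 12 / 5.21 − 1.96 = 0.34, power 0.63.
- A 12-point GMI × environment interaction: SE = 29.75 × √(4 / 65.2) = 7.37, and 12 / 7.37 − 1.96 = −0.33, power 0.37.

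These powers ignore any department differences.

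**4. Uncertainty of the cross-stratum contrasts.** The document gives no department ICC. Assume 0.01 to 0.05, the unadjusted SD of 29.75, and equally weighted departments. The error SD that department differences add to a 2 v 4 contrast is 29.75 × √ICC × √(1/2 + 1/4):
- ICC 0.01: 2.6 points
- ICC 0.025 (the plan's own value, which it uses for wing-level clustering): 4.1 points
- ICC 0.05: 5.8 points

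Recruiting more employees in the same departments does not reduce this. A model with wing clustering alone treats the 13 wings as independent. At best it would count the same variance as 29.75 × √ICC × √(1/6 + 1/7), which is 1.7, 2.6 and 3.7 points. So it understates the uncertainty if departments differ beyond wings.

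**5. Degrees of freedom.** With department as the unit, 6 − 2 = 4 df (critical t 2.78), compared with 13 − 2 = 11 (critical t 2.20) if wings are counted. There are C(6,2) = 15 ways to pick 2 of 6 departments. Even if the departments had been drawn at random, the smallest one-sided permutation p-value would be 1/15 = 0.067.

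**The case against.** The strongest reply is that nothing is hidden. The stratification is stated in the summary, in section 3.3 and in Appendix 1, and the phrase describing a randomised design carries that qualification in the same sentence. The stratified, pooled analysis is valid for the randomised question, and the sample size fits it. Model terms and contrast lists are commonly left to a statistical analysis plan. Section 6 already corrects for baseline, which would remove part of any stable department difference. All of this stands. It limits the point to the claims that go beyond GMI, but it does not answer it: no later analysis plan can make environment randomised, and the hypotheses and costed comparisons are fixed here without a caveat.

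A reader might infer more than the document supports:
- *That the two departments were hand-picked.* How they were selected is not stated. All that can be said is that no random step is described.
- *That employees knew their environment status when they consented.* Sections 3.4 and Appendix 3 do not establish this.
- *That every arm is hypothesised to beat control.* Section 2 speaks of the programme against control and, separately, of the combined arm against the single components.
- *That four-arm comparisons are absent altogether.* Section 6.1 takes four-arm mean differences in the primary outcomes for its ratio, and section 6 tests sick leave across arms. These rest on the same non-randomised contrasts and do not repair them.
- *That a bias or error of about 4 points has been shown.* It follows only from an assumed department ICC and a raw SD.

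**Conclusion.** The plan's randomised evidence concerns GMI v no GMI, including its two within-stratum forms, and that part is sound. Three further contrasts are not randomised, not labelled so, and not produced by the effectiveness analysis of need for recovery: combined v GMI-only, environment-only v control, and combined v control. They include half of the section 2 combination expectation and two of the three comparisons costed in section 6.1.

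This structural conclusion rests on the text alone. The size of the extra uncertainty does not: 2.6 to 5.8 points against the 12-point target depends on an assumed department ICC of 0.01 to 0.05 and an unadjusted SD, and would be smaller after the planned baseline correction. If departments do not differ beyond wings, that added error is nil, but the contrasts remain non-randomised.

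**What to change.** 1. In sections 2 and 6, name GMI v no GMI, stratified by environment, as the randomised confirmatory contrast.
2. For the other contrasts, specify one baseline-adjusted model for need for recovery with GMI, environment and GMI × environment.
3. Label environment-only v control, combined v control and combined v GMI-only as non-randomised and exploratory, for effects in section 6 and for costs in section 6.1.
4. State that, with 2 v 4 departments, the uncertainty of these contrasts must be judged at department level, for example by a sensitivity analysis with about 4 df. A department random intercept should not be the required solution, because six departments identify it only weakly.
5. Reword the section 2 hypotheses to match.

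The cost is some wording, one further model and one sensitivity analysis. No change to recruitment or allocation is needed. The price in interpretation is that conclusions on environment and on the combination over GMI alone become explicitly observational.
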